## Abstract

**Background: **Early access to rehabilitation can improve quality of life for those with life-limiting illnesses and is highlighted as a core component of the Adult Palliative Care Services Model of Care for Ireland. Despite this, palliative rehabilitation remains under-utilised and under-developed. In 2020, the Sláintecare Integration Fund provided opportunity to pilot a novel rehabilitative palliative care service, “Palliat Rehab”. This protocol proposes a case study, which aims to advance understanding of the form, content, and delivery of the pilot service.

**Methods: **A prospective, longitudinal, mixed-methods, case study design will be used to describe the service and to explore the experiences of patients, informal carers and clinicians. Additionally, data collection instruments will be tested and the utility of outcome measures will be examined. Data will be collected from documentary, survey, and interview sources.

Quantitative data will be analysed using descriptive statistics, including chi-square tests for categorical variables, Mann-Whitney U tests for ordinal data, and t-tests/ ANOVA for continuous data. Qualitative data will be analysed using thematic analysis.

**Conclusions: **New pathways are required to advance service provision to ensure that patients receive the ‘right care, in the right place, at the right time’. This protocol outlines a case study which will aim to develop current understanding of the implementation and delivery of a novel rehabilitative palliative care service in Ireland and will consider its potential contribution to the achievement of Sláintecare goals. Investigating the service within its environmental context will lead to a better understanding of ‘how’ and ‘why’ things happen. Findings will be used to inform efforts to further develop and tailor the intervention.

## Introduction

Rehabilitative palliative care has been defined as a paradigm integrating rehabilitation, enablement, self-management, and self-care into the model of palliative care to provide patients with support to enjoy the fullest possible life until death
^
3
^. The unmet rehabilitative needs of those with serious illness are increasingly recognised- that is, the need to be normal and in control, the need for better every day functioning and mobility, and the need to alleviate the fear of being a burden
^
4
^

Interventions adopting a rehabilitative palliative care approach can benefit individuals with life-limiting illnesses
^
48–
52
^. Specific studies have pointed to the benefit of an exercise programme for patients with cancer-related fatigue
^
6
^ and advanced non-small cell lung cancer
^
7
^. Recently, Nottelmann and colleagues conducted a randomised controlled trial of a novel, integrated rehabilitative palliative care programme for individuals newly diagnosed with advanced cancer and identified a benefit to their quality of life from the programme
^
8
^. These results are increasingly relevant in the Irish context, as the number of older people living with a palliative care need in Ireland is projected to increase by 89% between 2016 to 2046
^
1
^. This population will account disproportionately for disability burden, pain prevalence and health care use, leading to increased population health burdens and health care utilisation. It is estimated, for example, that there will be a 106% increase in requirement for the hours of healthcare delivered at home
^
1
^. As such, rehabilitative care offers an important way for the Irish health system to re-tool to meet these challenges, yet it is an under-developed component of palliative care for all adults receiving services in Ireland
^
2
^.

Though there may be substantial benefits to be gleaned from adopting a rehabilitative palliative care approach, difficulties implementing the approach have been noted internationally. In 2016, Thuesen and colleagues
^
5
^ conducted a literature review on the international evidence for coordination of rehabilitation and palliative care. This extensive review made notable recommendations for the implementation of rehabilitation in the palliative care approach, such as a coordinated programme that should be individualised to the needs of the patient, dynamically revised to suit their progress, and effectively assessed using outcome measures for all programme elements. Despite the growing evidence base for the benefits of offering rehabilitation programmes for individuals with palliative care
^
48–
52
^, the publication of Thuesen and colleagues
^
5
^ also highlighted substantial gaps in available guidelines for coordinating palliative care and rehabilitation in a single care approach. The authors concluded that there remained a lack of consensus on when and how rehabilitative palliative care should be offered and recommended that further research was required with regards to methods, activities, frameworks, and practical guidelines for service provision
^
5
^. As such, the current knowledge base on designing, coordinating, and delivering rehabilitative palliative care interventions remains incomplete and requires greater development to facilitate the coordination of these approaches.

### Rehabilitative Palliative Care in Ireland 

In Ireland, the few studies which have been conducted to date on palliative care rehabilitation have been descriptive or exploratory in nature
^
9–
11
^, and the only interventional study that has been published has focused on health and social care professional education
^
12
^. Rehabilitation was, however, highlighted in the Adult Palliative Care Services Model of Care for Ireland produced in 2019
^
2
^. The Adult Palliative Care Services Model of Care for Ireland recognises the importance of rehabilitative palliative care as a core part of service provision, while acknowledging the deficits that exist in staffing and development of services
^
2
^. The aim of the model of care is to ensure all individuals with a life-limiting illness in Ireland have access to the appropriate level of palliative care services to enhance their quality of life, irrespective of diagnosis and care setting. Included in the model of care is the optimal pathway of care for individuals with life-limiting illnesses, which entails a thorough needs assessment, initiating the correct care (e.g., specialist, generalist, integrated services), planning for ongoing and future care needs, engaging end-of-life care supports, and care for loved ones through the process of bereavement. Overall, the model of care acts as a guiding document for palliative care provision using eight core foundations to deliver an accessible and appropriate palliative care service.

Given the increasing demand for palliative care services in Ireland and the notable benefits of a rehabilitation approach in palliative care, greater coordination between palliative care and rehabilitation services is likely to prove a valuable approach in the health service. Greater integration of rehabilitation into palliative care in Ireland also aligns with the goals of healthcare reform in Ireland, as outlined in the Sláintecare Report. Established in 2017, Sláintecare is a ten-year reform programme in Ireland aimed at providing a more efficient and universal healthcare services, including the commitment to develop universal palliative care
^
13,
53
^. Responding to the urgent need to provide support to the healthcare system to test and scale ideas that meet Sláintecare goals, the Sláintecare Integration Fund was established in 2019. The Fund aims to support projects that:

Demonstrate innovative ways in which citizens can engage in their own health,Represent best practice in the management of chronic diseases and caring for older people, andEncourage innovations in shift of care to the community or promoting hospital avoidance.

Following application to the Fund, our team was awarded a grant to deliver an integrated rehabilitation service for patients with palliative care needs and to conduct an exploratory, longitudinal case study. The novel intervention draws on the core foundations of the Model of Care
^
2
^ as a means of enhancing research and innovation capacities in palliative care by examining the feasibility of providing the integrated service between hospital and community care settings. A description of each core foundation is available in the
*Extended Data,* accompanied by a brief outline of elements in the intervention drawing upon each one. The case study aims to advance understanding of the form, content, and delivery of the novel rehabilitative palliative care service (‘‘Palliat Rehab’’) in the provision of specialist palliative care for academic, policy and practice purposes.

### Objectives

This is a protocol for a case study which will examine a palliative rehabilitation intervention. The specific study objectives are:

To describe the novel rehabilitative palliative care service that spans hospital and community settings.To explore the experiences of patients, informal carers and clinicians while receiving or providing the service.To test data collection instruments and examine the utility of selected outcome measures.

## Methods

### Design

Guided by an exploratory case study framework
^
16
^, and adopting a post-positivist approach
^
17
^, this case study will examine the novel service, as delivered by one hospital organisation and one community-based organisation, for an 18-month period of service provision and will provide insight into the delivery of palliative care rehabilitation. ‘Palliat Rehab’ is a new service initiative, and a case study design was chosen because of the need to capture information to answer ‘how’, ‘what’ and ‘why’ questions using a naturalistic method
^
14
^. Case studies allow for investigation of a contemporary phenomenon within its real-life context when the boundaries between phenomenon and context are not clearly evident
^
14
^ and provide an in-depth, multi-faceted understanding of issues that can help develop or refine theory
^
15
^.

The scope of our study includes the rehabilitation service, the staff delivering the service, and the direct and indirect recipients of the service (patients and informal caregivers/family members). This study will comprise two components of data collection: a ‘concurrent’ component, where routine, quantitative data will be collected from participants during the intervention sessions, and a ‘phased’ component, where patients will be invited to contribute data on their experiences of Palliat Rehab using a quantitative survey and during semi-structured, qualitative interviews. Their informal caregivers and relevant staff members will also be invited to engage in semi-structured interviews on their views of the service as an additional element of the phased component. In doing so, the study will contribute to opening the ‘black box’ of palliative care rehabilitation interventions and provide transferable knowledge that will be of value to the future development of interventional studies of service delivery.

### Study setting

The rehabilitation service will be provided by the Mater Misericordiae University Hospital (Mater Hospital) and St Francis Hospice for an 18-month period.

The Mater Hospital is a 630-bed teaching hospital providing local services for its catchment population of Dublin’s north inner city and a range of specialist services on a regional and national level. St Francis Hospice Dublin is a specialist palliative care service organisation providing in-patient, out-patient, and home-based services to people with progressive, life-limiting illness in the North Dublin area. The rehabilitation service will be delivered by a hospital-based senior occupational therapist and a community-based senior physiotherapist, both of whom work as members of specialist palliative care teams.

### Eligibility Criteria

The case study will recruit participants from the specialist palliative care services of the Mater Hospital and the community palliative care services of St Francis Hospice Dublin. Overall, the following three groups of participants have been identified and will be recruited during this case study: patients who receive Palliat Rehab, informal caregivers/ family members of patients receiving the rehabilitation service, and staff engaging in either the design or delivery of Palliat Rehab.

For patients receiving palliative care in the Mater Hospital or in St. Francis Hospice, referral to Palliat Rehab will depend on a palliative needs assessment, where severe ill-health, symptom burden and/or cognitive deficit may preclude individuals from taking part. Needs assessments comprise holistic assessments of individual need that include, but are not limited to, assessment of physical condition, appraisals of pain, examination of function and mobility, discussion of potential difficulties completing activities of daily living, and identifying goals patients may have for their care. As rehabilitation needs can vary substantially between individuals and their conditions, however, inclusion will be determined on a case-by-case basis. If the specialist palliative team think that an individual has a rehabilitation need that could be met by the service, then the new service will be explained and offered to the patient by a team member. Specific eligibility criteria for each group have been highlighted in
Table 1, where criteria for patients refers to both the concurrent and phased components, and criteria for caregivers and staff refers to the phased component. 

**Table 1. T1:** Eligibility criteria for components of the study.

Patient inclusion criteria *Concurrent and phased components*	Caregiver inclusion criteria *Phased component*	Staff inclusion criteria *Phased component*
1. Receiving the novel palliative care rehabilitation service due to the identification of a rehabilitation need 2. ≥ 18 years of age 3. English speaking 4. Able to provide informed consent 5. Patients do not need a caregiver willing to participate in the study	1. Self-endorsing or identified by the patient as a primary caregiver 2. ≥ 18 years of age 3. English speaking 4. Able to provide informed consent 5. Caregivers related to a participating patient are eligible for inclusion if the above criteria are satisfied, regardless whether their loved one participates in the research element or receives the intervention only.	1. Identified as a clinical staff member who has been involved in the design and/or delivery of the palliative care rehabilitation service
Patient exclusion criteria	Caregiver exclusion criteria	
1. Unable to complete the study measures and/ or participate in an interview in the opinion of attending clinician. Patients may be unable to complete measures or participate due to ill-health, symptom burden or cognitive impairment.	1. Patient does not wish caregiver to be invited to participate in the study	

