### Outcomes

This case study will collect multiple outcome measures to describe the intervention, to explore the experiences of participants, and to assess the utility of particular quantitative measures for such an intervention. The quantitative outcome measures to be collected from consenting patient participants during the concurrent component are divided into three categories (demographic, service-usage, and health and symptom data) and are listed in
Table 2. By collecting these three categories of data, it is anticipated that this case study will be equipped to adequately describe the sample served, the experience of patients receiving the intervention, and the feasibility of embedding the service into the existing healthcare infrastructure using service-usage data. All quantitative data measures will be collected once following initial enrolment of each patient, with the exception of the Palliative Care Outcomes Collaborative (PCOC) scale, which will be collected at baseline during the first intervention session and repeatedly collected during each session thereafter.

**Table 2. T2:** Quantitative data and measures.

Demographic data	Service-usage data	Health and symptom data
1. Gender Identity 2. Age 3. Marital status 4. Primary diagnosis 5. Primary care network 6. Current living conditions including home supports	1. Response times between referral and service enrolment 2. The number, type, nd period of clinical interactions with the rehabilitative palliative care service 3. Length of hospital stay (for hospitalised patients only) 4. Whether re-admitted to hospital within 30-days of discharge or receipt of services enrolment 2. The number, type, and period of clinical interactions with the rehabilitative palliative care service 3. Length of hospital stay (for hospitalised patients only) 4. Whether re-admitted to hospital within 30-days of discharge or receipt of services	1. The Palliative Care Outcomes Collaborative (PCOC) scale ^ 22 ^ 2. Charlson Comorbidities Index (CCI) ^ 23 ^ 3. The Clinical Frail Scale ^ 24 ^ 4. Palmar Grip Strength 5. 5x Sit-to-Stand test ^ 25 ^

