### Concurrent Component

The aim of the case study is not to test the rehabilitation service, therefore it would not be appropriate to use traditional power calculations when considering sample size for the quantitative data collection component of the case study.
^
20
^ The purpose of quantitative data collection in the case study is to contribute to the understanding of care delivery and stakeholder experience and to test data collection instruments and examine the utility of selected outcome measures. Considering the issue of justification of sample adequacy, anonymised, routine data will be collected on all patients who receive the service. , and all eligible patients will be offered the opportunity to participate in survey data collection.

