### Data collection

Using a mixed-methods approach, multiple sources of quantitative data will be collected in a sequential manner. Quantitative data collection will take place from service commencement, while qualitative interviewing will take place at two points- approximately 4–6 months after commencement of the service and in the final two months of service provision.

**
*Quantitative data.*
** Quantitative measures will include data that is recorded as a necessary or usual part of palliative care or rehabilitative palliative care service provision during patient assessments in patient charts or electronic patient records. All quantitative measures are summarised in
Table 2 under three category headings: demographic data, service-usage data and, health and symptom data. Following the establishment of informed consent from patients, demographic, service use and health and symptom data necessary for the delivery of care will be collected by the service’s occupational therapist and/or physiotherapist. As part of the phased component, survey data on patient satisfaction will be collected on completion of engagement with the rehabilitation service intervention.

**
*Qualitative data.*
** Semi-structured interview schedules for the first set of interviews for each group of participants were developed using a five-step framework of design
^
26
^. The five steps are as follows: (1) identifying the prerequisites for using semi-structured interviews; (2) retrieving and using previous knowledge; (3) formulating the preliminary semi-structured interview guide; (4) pilot testing the guide; and (5) presenting the complete semi-structured interview guide. Interviews across all three participant cohorts may take place in person or remotely according to the participant’s preference. Only an audio recording will be made regardless of method of interview. Interviews are estimated to last approximately 30–40 minutes and protocols will be piloted with volunteers in St. Francis Hospice to ensure question clarity, in addition to monitoring time demand.

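### The ability-based exclusion in Table 1 covers both components, so foreseeable non-completers are lost from the data used to judge the measures, and it conflicts with the statement that routine data cover all recipients

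*Protocol article*

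**What the plan says.** The protocol article has one ability-based exclusion for patients, in Table 1: "Unable to complete the study measures and/ or participate in an interview in the opinion of attending clinician". The reasons follow: "Patients may be unable to complete measures or participate due to ill-health, symptom burden or cognitive impairment". The text that introduces the table fixes its reach, "where criteria for patients refers to both the concurrent and phased components".

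The third objective is "To test data collection instruments and examine the utility of selected outcome measures". The Limitations section gives this particular weight, because the clinical usefulness of function and mobility measures in specialist palliative care is still debated.

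Three other statements say whose quantitative data are collected, and they do not agree:

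- Sample size, Concurrent Component: "routine data will be collected on all patients who receive the service".
- Outcomes: "The quantitative outcome measures to be collected from consenting patient participants during the concurrent component" are those listed in Table 2.
- Data collection: "Following the establishment of informed consent from patients, demographic, service use and health and symptom data necessary for the delivery of care will be collected".

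**The concern.** Inability to complete a measure is itself evidence on that measure's utility. If patients expected to fail are kept out of the concurrent component, the sample is partly selected on the result that the third objective sets out to observe. The bias runs one way: the measures look more usable, and floor effects are harder to see. Grip strength and the 5x sit-to-stand are the most exposed of the five health and symptom measures in Table 2, because they are performance tests.

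The wording also joins two different abilities with and/or. A patient who could do every measure but could not manage an interview of about 30 to 40 minutes can be excluded from the quantitative data as well. Yet demographics, service use, comorbidity and frailty need neither a performance test nor an interview, and the Data collection section describes the quantitative measures as data recorded in the usual course of care.

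Finally, collecting data on all recipients is what the article offers as justification for the adequacy of the quantitative sample. If the exclusion applies, that justification does not hold as stated.

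**Working it through.** **Reading the sections together**

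1. The exclusion sits in Table 1, and the introducing text applies the patient criteria to both components. On its face it is therefore not an interview-only rule.
2. It is separate from the needs assessment, which governs referral to the service. The first inclusion criterion in Table 1 already requires that the patient is receiving the service, so the exclusion is a second filter on recipients. The caregiver criteria confirm that some recipients have the intervention only and are not research participants.
3. The Sample size section promises routine data on all recipients. Outcomes and Data collection tie the measures to consenting patients. The article does not say which statement governs, or whether there are two datasets.

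**Size, as an illustration only**

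The article states no completion rate, no expected quantitative sample and no screening share, so there is no figure of its own to reproduce. Let *p* be the true proportion of recipients able to complete a measure, and *s* the proportion of those unable whom the clinician foresees and excludes. Both are assumptions.

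Observed completion = p / [p + (1 − p)(1 − s)]

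For p = 0.60:

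- s = 0.50: 0.60 / (0.60 + 0.40 × 0.50) = 0.60 / 0.80 = 75%
- s = 0.75: 0.60 / (0.60 + 0.40 × 0.25) = 0.60 / 0.70 = 86%
- s = 1.00: 0.60 / 0.60 = 100%

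The same formula over a wider range:

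| True completion | s = 0 | s = 0.5 | s = 0.8 | s = 1 |
|---|---|---|---|---|
| 90% | 90% | 94.7% | 97.8% | 100% |
| 80% | 80% | 88.9% | 95.2% | 100% |
| 70% | 70% | 82.4% | 92.1% | 100% |
| 60% | 60% | 75.0% | 88.2% | 100% |

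The column s = 0 is the position without the exclusion: observed and true completion agree. Every other column is higher, and the gap widens as true completion falls.

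**The case against.** The strongest answer is that the Sample size section governs. It speaks of all recipients for routine data, then of eligible patients for the survey. That contrast could mean that eligibility limits only the consented research part. If so, non-completers are in the routine records and little is lost. This reading is possible, but Outcomes, Data collection and the stated reach of Table 1 point the other way, and nothing reconciles them. The statement is a reason to resolve the conflict; it does not remove it.

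Several other points stand and limit the concern:

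- The criterion speaks of the study measures in the plural. A reader might infer that failing a single test, such as the sit-to-stand, excludes a patient. The text does not say so.
- The and/or could be read component by component, especially as Recruitment lets patients take part in the concurrent component without the phased one. The wording permits this reading but does not state it.
- Only failures foreseen by the clinician are removed. Later non-completion, for example in the PCOC scale repeated at each session, can still be seen. Qualitative data, including clinician interviews, are a further source on the measures.
- Referral already filters out some very ill patients, so the additional loss among recipients may be smaller than the illustration.
- Completion rate is not a named outcome, and the study is exploratory with no completion threshold.

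**Conclusion.** The concern holds in a limited form. As written, the exclusion removes foreseeable non-completers from the quantitative evidence on a stated objective, can remove patients who only cannot be interviewed, and conflicts with the promise of routine data on all recipients. The direction of the bias is clear: the measures look more usable than they are.

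The size is unknown. The range from 75% to 100% for a true 60% rests on two assumed inputs, and the upper end needs perfect foresight by the clinician.

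A reader might go further and infer that the study removes all the failures that it needs to count. The documents do not support that: unforeseen and later non-completion remains visible, and the routine-data statement may yet bring in the excluded patients.

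**What to change.** - Apply ability to take part in the interview or survey to the phased component only.
- Remove ability to complete the measures as an exclusion from the concurrent component. Keep the consent, language and other inclusion criteria; the change is not a licence to enrol every recipient.
- Reconcile Eligibility Criteria with Table 1, Outcomes, Sample size and Data collection on whose data are collected, separating anonymised routine data from data that need consent.
- For each measure record completed, attempted but not completed, or not attempted with the reason. Report completion over all concurrent-component participants, and over all recipients where the anonymised routine data allow.
- According to Study status, collection began in February 2020. Count the patients already excluded under this criterion, with reasons, and state the selection when reporting on utility.

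The cost is a change of eligibility wording and slightly more recording. Completion figures will look less favourable.
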